### Sample Size

A convenience sample of 76 participants will be enrolled in the study. This sample size is based on the feasibility of recruitment over a 6-month time period and is not determined in order to be able to detect between-group differences. Approximately 750 unique ACS patients were discharged from the target hospital during the 2012/2013 fiscal year. In a preliminary feasibility survey of patients, 14 of 28 had mobile phones with texting capabilities. Assuming 40% are eligible and 50% agree to participate [32], we expect approximately 76 patients will agree to participate over 6 months of recruiting.

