### Randomization

After discharge and once the baseline assessment has been completed, participants will be randomized to receive either usual care or usual care plus the 60-day text messaging program (Txt2Prevent) using a 1:1 allocation ratio. To minimize bias, randomization will be conducted by a research assistant who is not involved in either the recruitment or data collection phases. This research assistant will use a Web-based randomization service developed through an independent research center. To ensure balance between the groups, the randomization will be stratified by sex and use block randomization with variable block sizes. The randomization research assistant will register participants for the TxT2Prevent intervention, when appropriate, and then contact all participants by phone to inform them of their group assignment. The start date for participants in the Txt2Prevent program will be documented. A letter will also be sent to all study participants’ primary care providers informing them that their patient has been enrolled in the study. Primary care providers will be identified by the participant. The primary care providers’ addresses will be obtained online from the registry maintained by the provincial licensing and regulatory body for physicians. Participants will be told to contact the research assistant who performs the randomization during the course of the study if they have any questions. Participants will be aware that the text messaging program is the intervention of interest as it is being compared to usual care.

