Secondary outcomes are health-related quality of life, cardiac self-efficacy, medication adherence, health care resource use, hospital readmissions, and mortality. Health-related quality of life will be measured by the EQ-5D-5L, a measure of health status developed by the EuroQol Group that comprises 5 dimensions (mobility, self-care, usual activities, pain/discomfort, and anxiety/depression; 1 item per dimension) with each item having 5 levels of response [36]. The Canadian EQ-5D-5L scoring algorithm will be used to value the health state descriptions reported by study participants [37]. Cardiac self-efficacy will be measured through a modified Sullivan Cardiac Self-Efficacy scale. The original scale has 13 items and is composed of 2 factors, control symptoms and maintain function. Responses are on a 5-point Likert scale where a higher number indicates more confidence. It has high internal consistency (Cronbach alphas of .90 and .87 for the 2 scales, respectively) and good convergent and discriminant validity when compared with other distress and disability scales [38]. The modified version combines 2 questions about symptoms and adds additional questions about diet and emotional distress. Medication adherence will be measured with the 8-item medication adherence scale developed by Morisky et al [39,40,41]. This medication adherence scale has good internal consistency (Cronbach alpha = .83) and reliability when assessed in a hypertensive population [39]. It has good sensitivity (93%) and moderate specificity (53%) [39]. Health care resource use over the 60-day follow-up period (ie, visits to health care practitioners, visits to a hospital, use of phone health services, cardiac rehabilitation program participation, out-of-pocket expenses, and medication use) will be self-reported by all study participants in a structured format using a questionnaire developed by the research team [42]. Self-report resource use questionnaires provide an efficient method of collecting information in the absence of routine data sources [42,43]. Although reliance on self-reported health care resource use may be regarded as a limitation, the 60-day follow-up period in this study is significantly shorter than timeframes that have been used extensively in economic evaluations performed alongside clinical trials. Hospital readmissions will be assessed through self-report and medical records. Mortality will be assessed through medical records. The EQ-5D-5L and cardiac self-efficacy scale will be measured both at baseline and follow-up while medication adherence and health care resource use will be measured only at follow-up.

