### Statistical Analyses

As this is a pilot study, we are not statistically powered to detect the magnitude of differences we will be looking for in the full trial. Nevertheless, we will undertake similar analyses to those we will use in the full trial and regard them as exploratory in nature. First, descriptive statistics will be used to characterize the sample. All variables will be analyzed for their distribution, and relevant transformations will be applied if distributions are nonnormal. For the primary outcome, change from baseline heiQ scores will be analyzed using multiple linear regression, using the intent to treat principle. The dependent variable will be the change from baseline heiQ scores while the independent variables will be group assignment, age, sex, and any clinically relevant baseline factors identified. Change in health-related quality of life and self-efficacy questionnaire scores and differences in medication adherence scores will be modeled in the same method as the primary outcome. Predictors of hospital readmissions and mortality will be analyzed with logistic regression while a survival analysis will be used to evaluate the time until event between the 2 groups using a Cox proportional hazards regression. Group assignment, age, and sex will be a priori covariates. Clinically relevant differences in baseline factors will be included as covariates in the models. Missing values will be addressed as per the guidelines provided with the questionnaires. SPSS (IBM Corp) will be used for statistical analysis. Statistical significance will be set at *P*<.05.

An economic evaluation will also be performed alongside the pilot trial, utilizing EQ-5D-5L and health care resource use data collected during the 60-day follow-up period. A cost-consequence analysis framework will be used as the base case economic evaluation [44,45] where resource use (and associated costs) and outcomes (eg, quality-adjusted life years [QALYs] generated from EQ-5D-5L responses) within the 2 study groups are listed, separately, in a disaggregated format. This type of evaluation makes no attempt to combine costs and effects into a single outcome measure (such as a cost-per-QALY ratio) and has particular value in aiding transparency. Canadian guidelines for the conduct and reporting of economic evaluations will be followed; publication of updated Canadian guidelines is expected in early 2017 [46].

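### QALYs are described only as a listing by group with no adjustment for baseline EQ-5D-5L utility named; adding a baseline-adjusted difference is a minor, nearly free gain in precision

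*Protocol article*

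**What the plan says.** The last paragraph of Statistical Analyses in the protocol article makes a cost-consequence analysis the base case. Costs and outcomes, with QALYs as the example outcome, are reported as "quality-adjusted life years [QALYs] generated from EQ-5D-5L responses) within the 2 study groups are listed, separately, in a disaggregated format". The paragraph gives no rule for turning utilities into QALYs. It neither names nor rules out an adjustment for baseline utility, and it plans no QALY test and no cost-per-QALY ratio. It refers to Canadian guidelines for economic evaluations, whose content is not shown.

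The paragraph before it analyses change in quality of life by linear regression on group, age, sex and relevant baseline factors. Baseline covariates are tied to those models.

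On measurement, Study Outcomes says: "The EQ-5D-5L and cardiac self-efficacy scale will be measured both at baseline and follow-up". Follow-up Assessment places the second measurement 60 days after randomisation.

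On design, Sample Size says: "A convenience sample of 76 participants will be enrolled in the study". That number "is not determined in order to be able to detect between-group differences". Allocation is made "using a 1:1 allocation ratio", and "the randomization will be stratified by sex and use block randomization with variable block sizes". Baseline utility is thus balanced only by chance, apart from whatever part of it goes with sex.

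**The concern.** With two utility values per person, a 60-day QALY is the average of the two multiplied by the time between them. The first value is taken before randomisation. An arm that happens to start healthier therefore shows more QALYs even if the programme does nothing.

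The planned change-score regression and the QALY listing treat baseline in opposite ways, so they can disagree. Suppose the text-message arm starts 0.06 higher in utility and ends 0.02 higher. Its change is then 0.04 worse, yet its QALY total is 0.0822 × (0.06 + 0.02) = 0.0066 better.

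At stake is how the economic results are read. The second study objective is comparative, the article says the full trial will use similar analyses, and the results are meant to inform that trial. Two raw QALY totals side by side invite a comparison that they support poorly, while the data for a sharper one are already collected.

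**Working it through.** **The plan's own figure.** Sample Size gives these inputs: "Approximately 750 unique ACS patients were discharged from the target hospital during the 2012/2013 fiscal year", recruitment over 6 months, and "Assuming 40% are eligible and 50% agree to participate". Then 750 × 0.5 × 0.40 × 0.50 = 75, which agrees with the stated 76 to within rounding. At 1:1 this is 38 per arm. The article gives no utility SD, correlation, target utility gain or QALY precision, so there is no QALY figure to reproduce.

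**Assumptions.** Two-point area rule; exactly 60 days; 38 per arm with complete data; the same utility SD at both times, 0.20 (range 0.10 to 0.25); baseline/follow-up correlation ρ = 0.5 (range 0.3 to 0.7).

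**Weight of baseline.** QALY = (u0 + u1)/2 × 60/365. Each utility value has weight k = 60/365/2 = 0.0822.

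**Chance imbalance, direct term.** SE of the baseline difference = SD × √(2/38).
- SD 0.20: SE 0.0459, so 1.96 × 0.0822 × 0.0459 = ±0.0074 QALY.
- SD 0.15: ±0.0055.
- SD 0.25: ±0.0092.

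**Comparator.** A true day-60 gain of 0.05 is worth 0.0822 × 0.05 = 0.0041 QALY.

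**How often imbalance exceeds the effect.** The direct term is k × D for a baseline difference D. Part of D also persists to day 60, so the full shift is k × (1 + ρ) × D. The chance that its absolute size exceeds the true effect is:

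| Assumption | Gain 0.03 | 0.05 | 0.08 | 0.10 |
|---|---|---|---|---|
| SD 0.20, direct term only | 51% | 28% | 8% | 3% |
| SD 0.20, with carry-over, ρ 0.5 | 66% | 47% | 25% | 15% |
| SD 0.10, with carry-over, ρ 0.5 | 38% | 15% | 2% | 0.4% |

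**Precision with and without adjustment.**
- Unadjusted SE = k × SD × √(2/38) × √(2(1 + ρ)) = 0.0822 × 0.0459 × √3 = 0.0065; 95% half-width 0.0128.
- Adjusted SE = k × SD × √(2/38) × √(1 − ρ²) = 0.0822 × 0.0459 × √0.75 = 0.0033; 95% half-width 0.0064.
- Ratio adjusted/unadjusted = √((1 − ρ)/2) = 0.59, 0.50 and 0.39 at ρ = 0.3, 0.5 and 0.7. The ratio does not depend on the SD or the sample size. With 30 per arm, as an allowance for loss, the SEs at ρ = 0.5 are 0.0074 and 0.0037.

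**Check by simulation** (20,000 trials, SD 0.20, ρ 0.5, true gain 0.05). The SEs were 0.0065 and 0.0033. Both estimators averaged 0.0041, the true value. The estimate had the wrong sign in 26% of trials unadjusted and 11% adjusted.

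**The case against.** The strongest reply is that the article never says the QALYs will be unadjusted. It is a condensed publication. The QALY rule and covariates commonly sit in a full protocol or an economic analysis plan, and the cited guidelines may cover them. Adjusted means could also be listed by group without contradicting the sentence quoted. This stands: a reader might infer that the plan rules out or rejects adjustment, and the text does not support that. What remains is that the article fixes the form of the QALY output as a listing and places baseline covariates only in regression models, and a listing is not a model.

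The second reply is that nothing inferential hangs on it. There is no QALY test and no ratio, the analyses are declared exploratory, and the main EQ-5D-5L comparison already works on change from baseline. This also stands, and it limits the weight of the point. It does not remove the benefit, because a small sample is where chance imbalance is largest.

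The third reply concerns size. A reader might infer that imbalance can swamp any plausible 60-day effect. The documents give no plausible effect and no SD, and the figures say otherwise: ±0.0074 QALY corresponds to a day-60 gain of 0.0074/0.0822 = 0.09, and ±0.0055 to about 0.067. Larger gains fall outside these ranges, and at SD 0.10 imbalance seldom exceeds a gain of 0.08.

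**Conclusion.** The point holds as a minor improvement. Under the two-point rule, at about 38 per arm, chance imbalance in baseline utility can match or exceed a small-to-moderate QALY effect. Adjusting for a value already collected would cut the standard error of the QALY difference by roughly 40% to 60% over the assumed correlations.

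It would be wrong to call the listed QALYs biased. Both the raw and the adjusted difference are unbiased over randomisations; the issue is precision, and how to read one trial in which the arms happen to start apart. All QALY sizes rest on an assumed SD, equal variances at both times and complete follow-up. The relative gain in precision also needs equal variances, and otherwise depends only on the correlation.

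**What to change.** Keep the disaggregated cost-consequence table as planned. Add to the economic paragraph:

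- the rule by which QALYs are calculated from the two utilities;
- the between-group QALY difference from a regression of each participant's 60-day QALY on group, baseline EQ-5D-5L utility, age and sex, with a 95% CI (bootstrap or robust);
- a statement that raw QALY totals by arm are descriptive and will not be interpreted comparatively.

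Baseline-adjusted arm means can stand beside the raw means in the same table. The cost is a few lines of text and one further regression on data already collected. Recruitment, assessments and trial conduct do not change.

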### Assessments

#### Baseline Assessment

When possible, the baseline assessment will be done as a face-to-face session prior to hospital discharge. In situations where the baseline assessment cannot be completed prior to discharge, it will be completed by phone or through an online survey within 7 days of discharge. The assessment will consist of the heiQ, EQ-5D-5L, and Cardiac Self-Efficacy questionnaires. Participants will also be asked demographic questions (age, sex, marital status, geographic location, employment status, education, and household income) and questions about their mobile phone (frequency of use, texting frequency, need for help or support, confidence in using, type of mobile phone, and ownership). Medical history (reason for admission, comorbidities, previous cardiac events, and smoking status) will also be obtained through a combination of self-report and medical record review. Trained assessors will be blinded as randomization will not occur until after the baseline assessment.

#### Follow-up Assessment

At 60 days following randomization, all participants will be contacted to complete a follow-up assessment. The assessment will consist of the readministration of the heiQ, EQ-5D-5L, and modified Cardiac Self-Efficacy Scale. Additionally, the Morisky Medication Adherence Scale (MMAS), health care resource use and smoking status questionnaire, and the readmissions and mortality assessment will be completed. All readmission events per participant will be recorded. The health care resource use questionnaire will be administered over the phone, while the other questionnaires (heiQ, EQ-5D-5L, Cardiac Self-Efficacy Scale, and MMAS) will be sent by surface mail, along with a $20 gift card. If the participant is unable or unwilling to complete the questionnaires by mail or phone or is unresponsive to our attempts at mail or phone contact, they will have the option to complete the questionnaires via an online survey. An approved online version of the EQ-5D-5L will be used (approval from the EuroQol Group), while the other outcome measures will be adapted to an online survey format and tested for user friendliness. The method for assessment will be documented in the study database. If the participant cannot be contacted, we will attempt to recontact every 3 to 5 days by using phone, mail, and email contact information. Participants will be considered lost to follow-up if the follow-up session is not completed within 6 weeks after the 60 days following randomization.

Participants who are randomized to the Txt2Prevent group will also be invited to participate in a semistructured phone interview after completion of the 60-day follow-up. Interviews are expected to be approximately 30 minutes and will be done at a different time than the follow-up assessments in order to avoid a lengthy phone call. Interview participants will be selected to cover a range of characteristics to represent the sample of study participants (eg, male/female, rural/urban, and different age groups). Participants will be asked to share their experiences of living with and managing their condition as well as their views on the text messaging program (eg, “Can you tell me about how you have managed your heart condition over the past 2 months?” and “Has the text messaging program impacted your life over the past 2 months? If so, how?”). Questions to evaluate the text messages will ask about the clarity, tone, and frequency of the messages; the duration of the program; what topics were the least or most helpful; and what proportion of messages they read. Interviews will be recorded and transcribed verbatim and analyzed through a general inductive approach [47]. Through an iterative process, categories and themes will be created by detailed reading and line-by-line coding. Interviews will continue until theme saturation occurs [48]. NVivo (QSR International) software will be used for qualitative analysis. The findings from the interviews will be valuable in providing the context for the quantitative findings and for assessing the acceptability of the intervention.

## Results

Ethics and institutional approval have been obtained from the Providence Health Care Research Ethics Board and Simon Fraser University’s Office of Research Ethics. Study staff have been hired and trained. Recruitment started in June 2015 and was completed by December 2016, with data collection being completed by January 2017.

## Discussion

### Summary

This study aims to evaluate whether a text messaging program can help support patients with ACS after their discharge from hospital. A randomized controlled pilot trial with semistructured interviews will be used to determine preliminary efficacy, feasibility, and acceptability. Although previous studies have looked at text messaging in CVD patients, no known studies have evaluated the use of text messages among patients with ACS during the hospital-to-community transition period, which is a high-risk time for readmission [6].

### Study Considerations

The Txt2Prevent study is an exploratory pilot study to assess preliminary efficacy, acceptability, and feasibility of a text messaging program to improve self-care and management in ACS patients after discharge, which leads to several study considerations. First, due to the nature of the intervention, the participants are not blinded. Additionally, it is difficult to create a suitable attention control, so the intervention group is being compared to usual care. Second, we are unable to objectively determine adherence or even if participants read the messages; however, we will ask participants about their experiences in semistructured interviews. Third, several of the outcomes are self-reported, which may introduce bias; however, the study will use common and validated measures.

### Conclusion

The Txt2Prevent study is a novel project to determine if text messaging can support ACS patients in the critical period immediately after discharge. We intend to use the results of the study to inform a larger clinical trial. If effective, the Txt2Prevent program has the potential to be translated into practice and be scaled up and implemented in clinical settings. Implementing the program on a larger scale is likely to be feasible because the program requires limited human resources and text messages are low cost. The study will contribute to our understanding of mHealth in health services research and will inform future studies on the use of text messaging to support ACS patients as they transition from hospital to home.

## Abbreviations

ACS: acute coronary syndrome
AMI: acute myocardial infarction
CIHR: Canadian Institutes of Health Research
CONSORT: Consolidated Standards of Reporting Trials
CVD: cardiovascular disease
heiQ: Health Education Impact Questionnaire
MMAS: Morisky Medication Adherence Scale
MSFHR: Michael Smith Foundation for Health Research
QALY: quality-adjusted life year

## Appendix

Multimedia Appendix 1 CIHR Peer Review.

Multimedia Appendix 2 CONSORT EHEALTH Check List.
